## Abstract

Although acute psychotic symptoms are often reduced by antipsychotic treatment, many patients with schizophrenia are impaired in daily functioning due to the persistence of negative and cognitive symptoms. Raloxifene, a Selective Estrogen Receptor Modulator (SERM) has been shown to be an effective adjunctive treatment in schizophrenia. Yet, there is a paucity in evidence for raloxifene efficacy in men and premenopausal women. We report the design of a study that aims to replicate earlier findings concerning the efficacy of raloxifene augmentation in reducing persisting symptoms and cognitive impairment in postmenopausal women, and to extend these findings to a male and peri/premenopausal population of patients with schizophrenia. The study is a multisite, placebo-controlled, double-blind, randomised clinical trial in approximately 110 adult men and women with schizophrenia. Participants are randomised 1:1 to adjunctive raloxifene 120 mg or placebo daily during 12 weeks. The treatment phase includes measurements at three time points (week 0, 6 and 12), followed by a follow-up period of two years. The primary outcome measure is change in symptom severity, as measured with the Positive and Negative Syndrome Scale (PANSS), and cognition, as measured with the Brief Assessment of Cognition in Schizophrenia (BACS). Secondary outcome measures include social functioning and quality of life. Genetic, hormonal and inflammatory biomarkers are measured to assess potential associations with treatment effects. If it becomes apparent that raloxifene reduces psychotic symptoms and/or improves cognition, social functioning and/or quality of life as compared to placebo, implementation of raloxifene in clinical psychiatric practice can be considered.

## Introduction

1

Schizophrenia is a common disorder, or rather a collection of several disorders, with heterogeneous combinations of symptoms and variable outcomes [1,2]. While remission of acute psychotic symptoms is achievable for the majority of patients with the use of current treatment options [3], a substantial group of patients remain symptomatic [[4], [5], [6]]. For example negative and cognitive symptoms, which are strongly related to functional outcome, can often persist [5,7]. It therefore remains important to improve pharmacotherapy, for example with augmentation strategies [6,8]. This report describes a study protocol for a novel augmentation strategy to reduce persistent positive, negative and cognitive symptoms and cognitive impairment in women and men with schizophrenia.

In schizophrenia, robust sex differences exist with an incidence risk ratio of 1.4 for men versus women [9,10]. Age of onset is significantly lower in men [2,11], while women show a second incidence peak around menopausal age [12,13]. Premenopausal women experience a more favourable course than men, with less psychotic and negative symptoms, better cognitive and social functioning and less hospitalisations [[14], [15], [16]] [[14], [15], [16]] [[14], [15], [16]]. Women experience less symptoms in the high estrogen phase of their menstrual cycle and higher estrogen levels are strongly correlated with better cognitive performance and lower symptom severity in women with schizophrenia [[17], [18], [19]] [[17], [18], [19]] [[17], [18], [19]]. In men and women with schizophrenia, the estrogen receptor is altered and its expression is lower than in healthy controls [20,21]. Therefore, the ameliorating and protective role of estrogen provides an important lead for new treatment strategies for schizophrenia [14,15,19,22,23].

Although the beneficial effect of estrogen augmentation in the treatment of symptom severity and cognitive impairment in schizophrenia is confirmed by clinical evidence [24], estrogen is not suitable for long term use due to its hazardous side effects on reproductive organs in both sexes and feminizing effects in men. Unlike estrogens, the Selective Estrogen Receptor Modulator (SERM) raloxifene has an estrogenic action in the brain, yet an antiestrogenic action in other tissues. Raloxifene could therefore have therapeutic benefits in patients with schizophrenia of both sexes.

A total of ten trials have been conducted that investigated raloxifene augmentation in schizophrenia, including predominantly postmenopausal women [[25], [26], [27], [28], [29], [30], [31], [32], [33], [34], [35]] [[25], [26], [27], [28], [29], [30], [31], [32], [33], [34], [35]] [[25], [26], [27], [28], [29], [30], [31], [32], [33], [34], [35]]. A recent meta-analysis revealed medium to large effect sizes (ES = 0.32–0.57) of raloxifene compared to placebo on symptom severity [36]. Several studies also suggest that raloxifene augmentation might have beneficial effects on domains of cognitive function [26,34,37,38]. To date, two trials were performed in men and pre/perimenopausal women and/or men [29,30]. Although these trials reported positive effects on symptoms [29] and cognition [30], the beneficial effects of raloxifene cannot be extrapolated to premenopausal women nor to men with schizophrenia without further testing. Such confirmation is essential before implementation of raloxifene in clinical practice can be advised.

In the current report, we describe the study protocol of a double-blind, randomised, placebo-controlled clinical trial examining the effects of 12 weeks of raloxifene augmentation (120 mg/day) on symptom reduction and cognitive improvement in men and pre-, peri- and postmenopausal women with a schizophrenia spectrum disorder. Other outcome measures include general and social functioning. Raloxifene augmentation is expected to reduce positive, negative and general symptoms and to improve cognitive, general and social functioning.

## Methods

2

This paper is written in line with the Recommendations for the Conduct, Reporting, Editing and Publication of Scholarly Work in Medical Journals (ICMJE) 2014 of the International Committee of Medical Journal Editors (IMCJE) [39]**.**

### Aims and objectives

2.1

The primary aim of this study is to investigate whether raloxifene augmentation compared to placebo is effective in reducing positive, negative and general symptoms and in improving cognitive functioning. Symptoms are measured by the positive and negative syndrome scale (PANSS) [40] and cognitive function is measured with the Brief Assessment of Cognition in Schizophrenia (BACS) [41]. The BACS consists of 6 tasks measuring different domains of cognitive functioning: list learning (verbal memory), verbal fluency (categorical instances and letter fluency, verbal fluency/processing speed), digit sequencing (working memory), symbol coding (processing speed), Token Motor Task (motor speed/processing speed), and the Tower of London Test (reasoning and problem solving).

Secondary outcome variables include general functioning, measured with the personal and social performance (PSP) [42]; severity of thought disorder, measured with the Thought And Language Disorder scale (TALD) [43]; health-related quality of life and quality adjusted life years (QALYs), measured with the EQ-5D-5L [31]; use of healthcare and non-healthcare resources, measured with the institute for Medical Technology Assessment's Medical Consumption Questionnaire (iMTA-MCQ) and Productivity Cost Questionnaire (iMTA-PCQ) respectively and depressive symptoms, measured with Beck's Depression Inventory (BDI) [32]. The Brief Negative Symptom Scale (BNSS) [44] is used to measure negative symptoms with a higher sensitivity [44].

Genetic, hormonal, and inflammatory biomarkers are assessed to predict treatment response. DNA-samples are collected in saliva. Serum hormonal biomarkers include for women prolactin, follicle-stimulating hormone (FSH) and 17β-estradiol, and for men prolactin, 17β-estradiol, free-testosterone and sex hormone-binding globulin (SHBG). Inflammation is measured as C-reactive protein (CRP) in serum.

Safety data are evaluated by comparing incidences of key Serious Adverse Events (SAEs) and Suspected Unexpected Serious Adverse Reactions (SUSARs) between groups, e.g. hospitalisations.

### Trial design and setting

2.2

Using a randomised double-blind placebo-controlled multicentre design, we assess the effect of raloxifene augmentation in patients with schizophrenia. After assessing in- and exclusion criteria (see section 2.4.1, 2.4.2), participants are randomised to either raloxifene or placebo treatment. The study is divided in two phases: (1) a treatment phase of 12 weeks and (2) a follow-up phase 2 years. The treatment phase consists of a baseline visit, a midterm visit (6 weeks post-baseline), and an end-of-treatment visit (12 weeks post-baseline). The follow-up phase consists of one visit (6 months post end-of-treatment visit), and two calls (at 12 months and 24 months post end-of-treatment visit). Study examinations scheduled in the course of the study are listed in Table 1. All assessments are performed by the study team, while the treating psychiatrist remains in charge of overall medical treatment. Participants continue their regular treatment during the trial, including antipsychotic medication. Any changes in treatment are recorded during each study call/visit.

**Table 1 tbl1:** Study procedures.

	Treatment phase				Follow-up phase			
	Visit 1	Call 1	Visit 2	Visit 3	Visit 4	Call 2	Call 3	*
	Baseline	Week 2 of treatment	Week 6 of treatment	End of treatment	Follow-up 6 months**	Follow-up 12 months**	Follow-up 24 months**	Early termination
**Week**	**0**	**2**	**6**	**12**	**38**	**64**	**116**	**-**
Informed consent, in-/exclusion criteria, MINI Plus	**x**							
Medical history, physical examination, presence/regularity of menses	**x**							
Use of concomitant medication	**x**	**x**	**x**	**x**	**x**	**x**	**x**	**x**
Daily functioning and hospitalizations						**x**	**x**	
Dispense study medication	**x**		**x**					
Side effects, compliance		**x**	**x**	**x**				**x**
Blood pressure	**x**		**x**	**x**				**x**
BMI calculation	**x**			**x**				
Smoking/drug/alcohol use	**x**		**x**	**x**				**x**
BACS, EQ-5D-5L, iMTA-MCQ/PCQ	**x**			**x**	**x**			**x**
PANSS, BNSS, TALD, BDI and PSP	**x**		**x**	**x**	**x**			**x**
Blood samples	**x**		**x**	**x**				**x**
DNA (saliva) sample	**x**							

* Early termination visit, performed when a patient prematurely discontinues the study. ** Calculated from end of treatment visit.

MINI, Mini International Neuropsychiatric Interview Plus; BMI, Body Mass Index; BACS, Brief Assessment of Cognition in Schizophrenia; EQ-5D-5L, EuroQol-5 dimensions 5 levels; iMTA-MCQ/PCQ, institute of Medical Technology Assessments' - Medical Consumption Questionnaire/Productivity Cost Questionnaire; PANSS, Positive And Negative Syndrome Scale; BNSS, Brief Negative Symptom Scale; TALD, Thought and Language Disorder Scale; BDI, Beck's Depression Inventory; PSP, Personal and Social Performance scale; DNA, Deoxyribonucleic acid.

### Ethical and regulatory standards

2.3

This study is performed according to the Declaration of Helsinki and the International Conference on Harmonization – Good Clinical Practice (ICH-GCP). Ethical approval was obtained from the research and ethics committee of the University Medical Center Utrecht (UMCU), protocol 16–103/G-M. The trial is registered in the ClinicalTrials.gov database (identifier NCT03043820) and the European Clinical Trials Database (EudraCT number 2015-004483-11). All study participants complete a written informed consent prior to participation and are eligible to receive other standard of care treatment.

### Study population and eligibility criteria

2.4

A total of 110 men and women with schizophrenia, schizoaffective or schizophreniform disorder, or psychotic disorder not otherwise specified (NOS) will be included. Recruitment takes place in both in- and outpatient facilities throughout the Netherlands (Institute for Mental Health Care Eindhoven (GGzE), Eindhoven; Psychiatric Center Geestelijke Gezondheidszorg Centraal (GGz Centraal), Amersfoort; UMCU, Utrecht; Reinier van Arkel Institute for Mental Health Care (RvA), ‘s-Hertogenbosch), and one clinic in Belgium (Ziekenhuis Netwerk Antwerpen, ZNA, Antwerp). Patients are approached by their treating psychiatrist and informed about the study by the multidisciplinary study team.

#### Inclusion criteria

2.4.1

1.Age ≥18 years;2.Capable of understanding the purpose and details of the study in order to provide written informed consent;3.DSM-IV diagnosis of: 295. x (schizophrenia, schizophreniform disorder, schizoaffective disorder) or 298.9 (psychotic disorder NOS);4.Stable dose of antipsychotic medication for at least two weeks;5.Women of childbearing potential (WOCBP, following menarche and until becoming post-menopausal unless permanently sterile after hysterectomy, bilateral salpingectomy and bilateral oophorectomy) who are sexually active must be willing and capable to use a non-estrogenic contraceptive (e.g. intrauterine device, cervical cap, condom or diaphragm) in case of sexual intercourse during the active treatment phase and at least four weeks after end of treatment6.Female patients with post coital uterine bleeding must have documented normal Papanicolaou-smear in the preceding five years. If no documented Papanicolaou-smear is present, patients must be willing to undergo one;7.Female patients between the ages of 52 and 75 must have a reported normal mammogram as part of the Dutch or Belgian breast cancer screening programme in the preceding two years. In case a patient has not participated in the regular breast cancer screening, these patients must be willing to undergo a mammogram.

#### Exclusion criteria

2.4.2

1.Pre-existing cardiovascular disease (not including hypertension);2.History of thromboembolic events;3.History of breast cancer;4.Familial tendency to form blood clots (such as factor V Leiden);5.Use of vitamin K antagonists;6.Use of cholestyramine or other anion exchange resins;7.Hypertriglyceridemia (triglycerides > 3 times the upper limit of normal (ULN));8.Liver function or enzyme disorders (serum bilirubin, alkaline phosphatase (AP), gamma-glutamyl transpeptidase (γ-GT), aspartate aminotransferase (ASAT) or alanine aminotransferase (ALAT) > 3 times the ULN as measured at baseline);9.Severe kidney failure (estimated glomerular filtration rate (eGFR) < 30 ml/min);10.Use of any form of estrogen, or androgen as hormonal therapy, or antiandrogen including tibolone or use of phytoestrogen supplements as powder or tablet in the past three months;11.For female patients: pregnancy or breast feeding (serum pregnancy test will be performed at all treatment visits for WOCBP).

### Study procedures

2.5

During the baseline visit, informed consent is signed and in - and exclusion criteria are checked. The Mini International Neuropsychiatric Interview 5.0.0 is administered to confirm the diagnosis [45]. If the patient is eligible for participation, he or she is randomised and study medication is dispensed. Blood is drawn at several time points to monitor kidney and liver function, lipids and hormone levels (for an overview of all laboratory measures, see Table 2). Furthermore, in WOCBP a pregnancy test is performed during each treatment visit. Two trained experienced researchers interview the patients at each visit using the PANSS and BNSS questionnaires. At all visits, a PSP score is determined and the severity of thought disorder and depressive symptoms is monitored using the TALD and BDI, respectively. Furthermore, side effects are checked and study medication count is conducted during each treatment visit. Cognitive testing, an assessment of quality of life and the use of healthcare and non-healthcare resources is performed at baseline, at end-of-treatment visit (12 weeks post-baseline) and at follow-up visit (6 months post end-of-treatment visit).

**Table 2 tbl2:** Overview of laboratory measures.

	Visit 1	Visit 2	Visit 3	*
	Screening	6 weeks of treatment	End of treatment	Early termination
**Week**	0	6	12	**-**
Kidney function (eGFR, creatinine)	**x**			
Liver enzymes and function (serum bilirubin, γ-GT, AF, ALAT, ASAT)	**x**	**x****	**x****	**x****
Triglycerides, total cholesterol, HDL- and LDL-cholesterol	**x**	**x****	**x**	**x**
CRP	**x**		**x**	**x**
Hormonal biomarkers	**x**		**x**	**x**
***for men:*** prolactin, 17β-estradiol, free testosterone, SHBG				
***for women:*** prolactin, FSH, β-HCG, 17β-estradiol				
β-HCG***	**x**	**x**	**x**	**x**

* performed if a patient prematurely discontinues the study. ** Performed when levels are above the upper limit of normal at baseline. ***Only for WOCBP. LHT, lithium heparin tube; SCT, sodium citrate tube; SST, serum separator tube; eGFR, estimated glomerular filtration rate; ASAT, aspartate aminotransferase; ALAT, alanine aminotransferase; γ-GT, gamma glutamyl transpeptidase; AF, alkaline phosphatase; HDL, high-density lipoprotein; LDL, low-density lipoprotein; CRP, C-reactive protein; APTT, activated partial thrombin time; FSH, follicle stimulating hormone; SHBG, sex hormone-binding globulin; β-HCG, beta-human chorionic gonadotropin

All researchers are trained to conduct the PANSS by a combination of instructional videos and assessment of a test video. Proper conduct of all other rating scales used for this study is trained by experts. Study members are trained regarding Good Clinical Practice. For each participant, visits are conducted by the same study-members.

#### Patient withdrawal

2.5.1

In case of drop-out during the treatment phase, an early termination visit similar to the end of treatment visit will be performed to finalise participation (Table 1). If the patient is not willing to complete all measures, priority will be given to the PANSS. Possible reasons to terminate a patient's participation in the trial include:•The patient withdraws his/her consent;•The patient is intolerant to the study drug;•The patient receives coercive treatment (based on judicial ruling);•The patient develops severe kidney failure (eGFR < 30 ml/min), hypertriglyceridemia (>3 times the ULN) or liver disease (defined as serum bilirubin, AP, γ-GT, ASAT or ALAT > 3 times the ULN);•The patient becomes pregnant;•Emergence of one or more contraindications against the study drug;•The investigator considers a patient's continued participation in the study to be unjustifiable on medical grounds (i.e., because of side effects or unusual risks).

If a patient discontinues treatment due to any of the above reasons, the patient receives treatment as usual in normal practice.

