### Safety

2.7

Medical history and current medication use are checked at baseline and treatment visits. Blood is screened at baseline for triglycerides, cholesterols, kidney and liver function. If a moderate elevation of triglycerides or liver enzymes is found (<3 times the ULN), these parameters will be measured at each treatment visit.

Physical examination is performed at baseline (visit 1) and end of treatment (visit 3), and blood pressure is measured at baseline and every treatment visit, as hypertension is a known side effect of raloxifene. Pregnancy tests are performed in all WOCBP, at baseline and every treatment visit. In case a patient reports any side effects at any time-point, thorough physical examination will be conducted at the earliest convenience. Furthermore, if appropriate, blood will be drawn. Study continuation or termination is based on the exclusion criteria 7 to 11 as defined in section 2.4.2.

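### Kidney and liver limits can end a patient's participation, but after baseline no kidney test is scheduled for anyone and no liver test for patients whose liver values were normal at baseline

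*Protocol article*

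**What the plan says.** All references are to the protocol article.

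- **Section 2.5.1 (Patient withdrawal)** gives this as one of the possible grounds for ending participation: "The patient develops severe kidney failure (eGFR < 30 ml/min), hypertriglyceridemia (>3 times the ULN) or liver disease". The liver ground is then defined as any listed liver value above three times the upper limit of normal (ULN).
- **Section 2.7 (Safety)** adds: "Study continuation or termination is based on the exclusion criteria 7 to 11 as defined in section 2.4.2". Criterion 8 is the liver limit and criterion 9 the kidney limit.
- **Section 2.5 (Study procedures)** states: "Blood is drawn at several time points to monitor kidney and liver function, lipids and hormone levels". It refers to Table 2 for the overview of laboratory measures.
- **Table 2**: the row that begins "Kidney function (eGFR, creatinine" is marked at week 0 and nowhere else. The liver row is marked at week 0, and at week 6, week 12 and early termination with a footnote: "Performed when levels are above the upper limit of normal at baseline".
- **Section 2.7** describes the same scheme in prose: "Blood is screened at baseline for triglycerides, cholesterols, kidney and liver function", followed by "If a moderate elevation of triglycerides or liver enzymes is found (<3 times the ULN), these parameters will be measured at each treatment visit". No kidney repeat is mentioned.
- For a patient who reports a side effect, section 2.7 provides for a physical examination and adds that "if appropriate, blood will be drawn". It does not say which tests would be run.

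**The concern.** A limit that a patient may reach during treatment is useful only if someone can see that it has been reached. Sections 2.5.1 and 2.7 set such limits for kidney and liver, and section 2.5 reads as if both organs were followed over time. The printed schedule does not do this for the kidney in any patient. For the liver it does so only in patients who were already abnormal, so it misses new injury in someone who started normal.

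The second box of study medication is handed out at week 6 (section 2.6.2). Under Table 2 that happens without a current eGFR for anyone and without a current liver value for patients normal at baseline. Section 2.6.3 gives observing risk in men and premenopausal women as a reason for the 12-week duration, and makes longer trials depend on showing that the dose is safe in them. What is at stake is patient safety and the basis for that statement, not the efficacy analysis.

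**Working it through.** The plan gives no figure to reproduce. The check compares each on-study limit with the tests that could reveal it.

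**Step 1. Scheduled tests for the limits in exclusion criteria 7 to 11** (Table 2; Table 1 for medication):

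| Limit | Week 0 | Week 6 | Week 12 | Early termination |
|---|---|---|---|---|
| Triglycerides (7) | all | only if raised at baseline | all | all |
| Liver panel (8) | all | only if raised at baseline | only if raised at baseline | only if raised at baseline |
| eGFR/creatinine (9) | all | none | none | none |
| Hormone use (10), via concomitant medication | all | all | all | all |
| Pregnancy (11) | women of childbearing potential | same | same | same |

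Kidney is the only limit with no scheduled check after baseline. Liver has none for patients normal at baseline. Triglycerides are not part of this point, because everyone has a value at week 12 or early termination.

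**Step 2. Count per completer.** Post-baseline kidney tests: 0. Post-baseline liver tests: 0 if normal at baseline, 2 (weeks 6 and 12) if raised.

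**Step 3. Is this an extraction fault?** Unlikely. The CRP and hormone rows keep their empty week-6 cells in the right place. Section 2.7 independently describes a baseline screen with repeats only for raised triglycerides or liver enzymes.

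**Step 4. Which visit could serve the rule?** Dosing lasts 12 × 7 = 84 days. A week-12 result arrives as dosing ends, and an early-termination result arrives after the patient has stopped. Only week 6 can lead to withdrawal during dosing. A week-6 test cuts the longest dosing stretch without a scheduled test from 84 to 6 × 7 = 42 days.

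**Step 5. Added assays at week 6.** Let N = 110 and let r be the share with a raised liver value at baseline (not given; assumed 0 to 0.5).

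- Kidney: N = 110.
- Liver: N(1 − r) = 110 at r = 0; 99 at r = 0.1; 55 at r = 0.5.
- Total: 220, 209 and 165. The maximum is 220.

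**Step 6. Extra draws at week 6.** Table 1 marks a week-6 blood sample for all. Under Table 2, a patient who is not of childbearing potential and has normal liver and lipid values has no week-6 assay. If Table 1 governs, no extra draws are needed. If Table 2 governs, the number is N(1 − w)(1 − q), where w is the share of childbearing potential, q is the share with any raised baseline value, and the two are taken as independent. Neither share is given. Assuming w = 0.1 and q = 0.1, the number is 110 × 0.9 × 0.9 = 89. Assuming w = 0.4 and q = 0.5, it is 110 × 0.6 × 0.5 = 33.

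**The case against.** The strongest reply is that this is a deliberate, risk-adapted scheme. Everyone is screened, patients beyond the limits are excluded, raised liver and triglyceride values are repeated, and anyone reporting a side effect is examined. Side effects are asked about at weeks 2, 6 and 12, and a data and safety monitoring board reviews the data annually. The section 2.5.1 grounds are introduced as possible reasons, and others on that list have no laboratory test either.

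Much of this is fair. The grounds in section 2.5.1 are permissive, and routes to detection do exist. A reader might infer that a breach could never be found; the documents do not support that. But each of those routes needs a symptom, a clinician's suspicion or a test done outside the trial. The board cannot review values that were never measured. Section 2.7 also words the link to the criteria more firmly than section 2.5.1 does.

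A second reply is that the article may condense a fuller laboratory table. The legend of Table 2 defines sample tubes and a clotting test that the table does not contain. Table 1 and Table 2 also differ on week-6 blood. It therefore cannot be excluded that the full protocol has kidney repeats. Against this, the prose of section 2.7 matches Table 2, so a lost table entry is not the likely explanation.

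A third reply is that the documents name no kidney or liver injury from raloxifene. That stands, and it limits what can be claimed about harm.

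**Conclusion.** The mismatch is real and worth correcting. The plan sets on-study kidney and liver limits and describes follow-up of both organs. It schedules no post-baseline kidney test for any of the 110 patients and no post-baseline liver test for those normal at baseline. A symptomless breach during the 84 days of dosing would come to light only by an unscheduled draw or through routine care.

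A reader might go further and put a probability on a missed breach, or conclude that patients are being harmed. The documents give no rate of such injury, so any figure would rest on an invented one, and none is offered. Nor does the point touch sample size, power, alpha or the primary outcomes. It rests on reading Table 2 as printed, which section 2.7 supports.

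**What to change.** In Table 2, add eGFR/creatinine for all patients at week 6 and remove the baseline condition from the week-6 liver panel. Run both on the blood sample that Table 1 already marks for that visit, with the result reviewed before or around dispensing of the second box. Align the wording as well: section 2.7 refers to criterion 8, which is tied to the baseline measurement, and should point instead to the on-study liver definition in section 2.5.1.

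**Cost.** At most 220 added assays, and fewer if many patients already have liver repeats. No extra draws are needed if Table 1's week-6 sample is taken from everyone. Otherwise some patients need one: 33 to 89 under the assumed shares above. The trial is recruiting in two countries, so the amendment has an administrative cost too.

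**Optional.** The same assays could be run at week 12 and early termination, where Table 2 already requires blood from everyone for lipids, CRP and hormones. That would serve safety description and follow-up of abnormal values, not the withdrawal rule. Its yield is limited: no breaches among 55 tested raloxifene patients would still leave a one-sided 95% upper bound of 1 − 0.05^(1/55) = 5.3%.

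**Cheaper alternative.** Restate the grounds as applying to clinically prompted results and correct the sentence in section 2.5. This needs no assays and makes the text consistent, but symptomless breaches stay unseen. If the full protocol already schedules these tests, correcting the article is enough.
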